### **6.11 Serious Adverse Events (SAE)**

An SAE is defined as any event that

- Results in death;
- Is life-threatening\*;
- Requires hospitalisation or prolongation of existing inpatient's hospitalisation\*\* (not applicable to planned EndoBarrier implant and explant procedures both requiring hospitalisation);
- Results in persistent or significant disability or incapacity;
- Is a congenital abnormality or birth defect;

|                                                                                   |                                                                                                  |                                           |                                                             |                                                  |
|-----------------------------------------------------------------------------------|--------------------------------------------------------------------------------------------------|-------------------------------------------|-------------------------------------------------------------|--------------------------------------------------|
| [figure not shown] | Title:
EndoBarrier TM
Gastrointestinal Liner
Diabetes Trial | Protocol No:
Version 5.0 | Sponsor:
Imperial College
London | Date:
5th March 2018 |
|-----------------------------------------------------------------------------------|--------------------------------------------------------------------------------------------------|-------------------------------------------|-------------------------------------------------------------|--------------------------------------------------|

\* “Life-threatening” in the definition of “serious” refers to an event in which the subject was at risk of death at the time of the event; it does not refer to an event which hypothetically might have caused death if it were more severe.

\*\* “Hospitalisation” means any unexpected admission to a hospital department. It does not usually apply to scheduled admissions that were planned before study inclusion or visits to casualty (without admission).

Medical judgement should be exercised in deciding whether an adverse event/reaction is serious in other situations. Important adverse events/reactions that are not immediately life-threatening, or do not result in death or hospitalisation but may jeopardise a subject, or may require intervention to prevent one of the other outcomes listed in the definition above should also be considered serious.

## 6.12 Serious Adverse Device Effect (SADE)

A Serious Adverse Device Effect (SADE) is an adverse device effect that has resulted in any of the consequences characteristic of a serious adverse event or that might have led to any of these consequences if suitable action had not been taken or intervention had not been made or if circumstances had been less opportune.

### 6.12.1 Anticipated Serious Adverse Device Effect (ASADE)

A serious adverse device effect which by its nature, incidence, severity or outcome has been previously identified in the risk analysis report or Clinical Investigation Brochure.

#### 1. During the implant procedure, ASADE's may include:

- GI Tract Laceration
- Oropharyngeal Perforation
- Oesophageal Perforation
- Gastric Perforation
- Bowel Perforation
- Bleeding
- Aspiration
- Infection
- DVT
- Cholecystitis/Cholelithiasis
- Pancreatitis with or without bile duct blockage

#### 2. During the implant period, ASADE's may include:

- Small Bowel Obstruction
- Implant Migration
- Bezoar
- Erosion
- Bleeding

|                                                                                   |                                                                                                  |                                           |                                                             |                                                  |
|-----------------------------------------------------------------------------------|--------------------------------------------------------------------------------------------------|-------------------------------------------|-------------------------------------------------------------|--------------------------------------------------|
| [figure not shown] | Title:
EndoBarrier TM
Gastrointestinal Liner
Diabetes Trial | Protocol No:
Version 5.0 | Sponsor:
Imperial College
London | Date:
5th March 2018 |
|-----------------------------------------------------------------------------------|--------------------------------------------------------------------------------------------------|-------------------------------------------|-------------------------------------------------------------|--------------------------------------------------|

Hypoglycaemia  
 Hyperglycaemia  
 Nausea/vomiting  
 Gastric or Bowel Perforation  
 Cholecystitis/ Cholelithiasis  
 Liver abscess (1% incidence)  
 Pancreatitis with or without bile duct blockage

*3. During and after the explant, ASADE's may include may include:*

GI Tract Laceration  
 Oropharyngeal Perforation  
 Esophageal Perforation  
 Gastric Perforation  
 Bowel Perforation  
 Bleeding  
 Aspiration  
 Adynamic Ileus  
 Infection  
 Cholecystitis/Cholelithiasis  
 Pancreatitis with or without bile duct blockage

#### **6.12.2 Unanticipated Serious Adverse Device Effect (USADE)**

Serious adverse device effect which by its nature, incidence, severity or outcome has not been identified in the current version of the risk analysis report or Clinical Investigation Brochure.

#### **6.12.3 Serious Public Health Threat**

Any event type which results in imminent risk of death, serious deterioration in state of health, or serious illness that requires prompt remedial action. This would include:

- a. events that are of significant and unexpected nature such that they become alarming as a potential public health hazard
- b. the possibility of multiple deaths occurring at short intervals."

#### **6.13 Reporting of SAEs**

Rapid reporting of all SAEs, occurring during the study or within 30 days following the completion of the study by the subject, must be performed as detailed in SAE reporting instructions. An SAE form should be completed and emailed to the CI for all SAEs within 24 hours of the sites knowledge. The CI or delegate will inform the sponsor of all SAEs within 24 hours of receiving notice of them. Additional information should be sent to the CI and sponsor within 5 days if the reaction has not resolved at the time of reporting. All unexpected SAEs should be recorded on the annual safety reports that are sent to REC on the anniversary of the date a favourable opinion for the study was given.

|                                                                                   |                                                                                                  |                                           |                                                             |                                                  |
|-----------------------------------------------------------------------------------|--------------------------------------------------------------------------------------------------|-------------------------------------------|-------------------------------------------------------------|--------------------------------------------------|
| [figure not shown] | Title:
EndoBarrier TM
Gastrointestinal Liner
Diabetes Trial | Protocol No:
Version 5.0 | Sponsor:
Imperial College
London | Date:
5th March 2018 |
|-----------------------------------------------------------------------------------|--------------------------------------------------------------------------------------------------|-------------------------------------------|-------------------------------------------------------------|--------------------------------------------------|

The Sponsor shall inform the device manufacturer (GI Dynamics) in writing about all unanticipated SAEs and incidents in writing within 24 hours. All anticipated SAEs shall be reported to GI Dynamics (GID) in writing within 7 calendar days.

The manufacturer is responsible to report any incidents and/ or unanticipated SAEs to the regulatory authority (MHRA) in compliance to the applicable regulation. GI Dynamics will perform the determination of Vigilance reporting based upon the requirements defined in the current version of MEDDEV 2 12.1.

Reporting timelines (device manufacturer to the MHRA) include:

1. 10 days for incidents and unanticipated SAEs indicating imminent risk of death, serious injury, or illness and require prompt medical reaction
2. 30 days for other reportable events

The sponsor shall supply GID all requested information to perform a comprehensive investigation of the incident and/ or SAE. This may include but is not limited to:

- Dates of occurrence
- Address and contact information of research site
- Patient identifier e.g. patient number, gender, age
- Full description of the event including symptoms, tests performed, treatments rendered, and final patient status at release
- Preconditions or concurrent medications that may have contributed to the event.
- Results of tests including but not limited to microbial isolates, endoscopic evaluations, CT scans, etc.
- Product return (EndoBarrier sleeve), using a return kit for package, for further analysis
- Swab samples of the device to be used in further analysis including DNA sequencing
- Hospitalization period
- Patient and physician compliance with the Instruction for use
- Other information that may be pertinent to the investigation

The request for the above information may occur as a request to complete GI Dynamic's form (F-070), email communication, or verbally.

The sponsor will retain the device in an unadulterated state, to allow for further sampling until provided a product disposition by GID. GID shall make the decision regarding need for device return within 20 calendar days.

The above information is forming part of the contract (amendment 1) with GID.

## **7 EARLY DISCONTINUATION OF THE STUDY OR INDIVIDUAL SUBJECTS**

### **7.1 Early Discontinuation of the Study**

The sponsor and/or Ethics Committee and/or government agencies may also request to stop enrolment of additional subjects for the study or an individual site for any reason. If the study enrolment is ended before the planned completion, subjects with a device implanted will be evaluated to determine if it is acceptable to leave the device in place and continue to follow the Schedule of Events.

|                                                                                   |                                                                                                  |                                           |                                                             |                                                  |
|-----------------------------------------------------------------------------------|--------------------------------------------------------------------------------------------------|-------------------------------------------|-------------------------------------------------------------|--------------------------------------------------|
| [figure not shown] | Title:
EndoBarrier TM
Gastrointestinal Liner
Diabetes Trial | Protocol No:
Version 5.0 | Sponsor:
Imperial College
London | Date:
5th March 2018 |
|-----------------------------------------------------------------------------------|--------------------------------------------------------------------------------------------------|-------------------------------------------|-------------------------------------------------------------|--------------------------------------------------|

In case of early discontinuation of the study, the follow-up visit (Visit 12 at 15 months) assessments should be performed for each subject, as far as possible. Subjects that have the device removed before Month 3 will return for the End of Treatment/Month 12 (visit 11). Subjects that have the device removed after Month 3 will return for the End of Treatment/Month 12 (visit 11), Month 15 (visit 12), Month 18 (visit 13) and Month 24 (visit 15) post explant follow-up visits.

## 7.2 Early Discontinuation of Individual Subjects

Subjects may discontinue study treatment (EndoBarrier) for the following reasons:

- At the request of the subject.
- If the investigator considers that a subject's health will be compromised due to adverse events or concomitant illness that develops after entering the study.

Any subjects who withdraw from the study that have the device implanted will have the device removed as soon as it can be arranged. Subjects that have the device removed before Month 3 will return for the End of Treatment/Months 12 (visit 11). Subjects that have the device removed after Month 3 will return for the End of Treatment/Month 12 (visit 11), Month 15 (visit 12), Month 18 (visit 13) and Month 24 (visit 15) post explant follow-up visits.

All subjects (including both control and device arm) who withdrew from the study early (either prior or after their treatment started – visit 4), and where no follow-up visit has been agreed or arranged as part of the previous protocol version (V4.1), will be contacted over the phone by the study team to ask for their permission (verbal consent documented by the study doctor using a specific form filed in the medical records) to perform a short telephone consultation at Month 24 (equivalent to visit 15). Data collected during this visit will include:

- HbA1 (provided through their last routine appointment at their GP)
- Body weight in kg
- Adverse events (section 6)
- Medical history/medication changes (section 5.5.4)

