### 5.5.10 Routine biochemistry and haematology

Blood samples will be obtained at all visits (except visit 2 and 4) after an 8 hour fast and processed by the local laboratory at Imperial College London NHS Trust or at University Hospital Southampton NHS Foundation Trust using standard methods' for routine tests. Patients can take their regular morning medications but are asked that they do not take any of their diabetes medications/oral hypoglycaemics on the morning of their study visit. Patients should bring their regular medication along to their study visits to be further advised by the doctor. See table below for a detailed description of blood collection at each visit:

|                                                                                   |                                                                             |                                    |                                               |                                            |
|-----------------------------------------------------------------------------------|-----------------------------------------------------------------------------|------------------------------------|-----------------------------------------------|--------------------------------------------|
| [figure not shown] | Title:
EndoBarrier TM
Gastrointestinal Liner
Diabetes Trial | Protocol No:
Version 5.0 | Sponsor:
Imperial College
London | Date:
5 th March 2018 |
|-----------------------------------------------------------------------------------|-----------------------------------------------------------------------------|------------------------------------|-----------------------------------------------|--------------------------------------------|

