**Table 4. Summary of blood tests at each study visit**

| Blood test                                             | V1 | V3 | V5 | V6 | V7 | V8 | V9 | V10 | V11 | V12 | V13 | V14 | V15 |
|--------------------------------------------------------|----|----|----|----|----|----|----|-----|-----|-----|-----|-----|-----|
| Haematology (Full blood count)                         | x  | x  | x  | x  | x  | x  | x  | x   | x   | x   | x   | x   | x   |
| Routine Biochemistry (including Urea and Electrolytes) | x  | x  | x  | x  | x  | x  | x  | x   | x   | x   | x   | x   | x   |
| Liver Function test                                    | x  | x  | x  | x  | x  | x  | x  | x   | x   | x   | x   | x   | x   |
| Fasting glucose                                        | x  | x  | x  | x  | x  | x  | x  | x   | x   | x   | x   | x   | x   |
| Creatinine                                             | x  | x  | x  | x  | x  | x  | x  | x   | x   | x   | x   | x   | x   |
| HbA1C                                                  | x  |    | x  |    | x  | x  | x  | x   |     | x   | x   |     | x   |
| Lipids (cholesterol, HDL, LDL, triglycerides)          | x  | x  | x  | x  | x  | x  | x  | x   |     | x   | x   | x   | x   |
| C-Peptide                                              | x  |    |    |    |    |    |    |     |     |     |     |     |     |
| Insulin                                                | x  | x  | x  |    |    | x  |    | x   |     |     |     | x   |     |
| Vitamin D                                              | x  |    |    |    |    | x  |    | x   |     |     |     |     |     |
| Iron studies                                           | x  |    |    |    |    | x  |    | x   |     |     |     |     |     |
| Vitamin B12                                            | x  |    |    |    |    | x  |    | x   |     |     |     |     |     |
| Serum Folate                                           | x  |    |    |    |    | x  |    | x   |     |     |     |     |     |
| Free Thyroxine                                         | x  |    |    |    |    |    |    | x   |     |     |     |     | x   |
| TSH                                                    | x  |    |    |    |    |    |    | x   |     |     |     |     | x   |
| Cortisol (Sub-group 1 only)                            |    | x  |    |    |    | x  |    |     |     |     |     |     |     |

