Conservatively, it was estimated that 15% of patients in the control arm will achieve the target but believe this to be an overestimate. The Steno study  is the best quality randomised study (80 patients in each arm) into the effect of best medical therapy published to date and demonstrated over an average 7.8 years significant improvements in HbA1c amongst those having intensive medical therapy from 8.4+/- 1.6 to 7.7+/-1.2, but no change in HbA1c amongst those continuing with standard medical therapy. This study defines the very best that could realistically be achieved in the control arm, but expect there to be very little if any change in this group. The reporting of HbA1c as an outcome measure was not in accordance with the newly defined IDF criteria, but considering the small average reduction achieved in the Steno study, it will be assumed that a target of 15% of patients reaching the endpoint is a conservative estimate. Company data on the small number of patients who have reached a year with the device in place suggest that 40% will achieve this target.

According to our own experience with the device in the commercially sponsored study, up to 30% of patients in the treatment group may have the device removed early. Nevertheless other commercially sponsored (unpublished) studies of this device have achieved lower explant rates ([name] – GI Dynamics). We have therefore diluted the treatment effect from 40% vs. 15% to 35% vs. 15% achieving the target of 20% reduction in HbA1c for treatment arm vs. standard arm. 73 patients per group will give 80% power to detect a significant effect. Adding 10% loss of follow-up increases the sample size to 80 per group.

The dilution was calculated starting from the assumption that 40% of patients with the device will reach the target (this estimate is based on company data based on diabetic patients in the same range of BMI as in the present proposal). If 30% of patients in the treatment group need to remove the device early but remain available for follow-up, in the worst case scenario, the proportion reaching the target is the same as in the control group, bringing the estimate for the treatment group to 32.5%. However most of them will keep the device for some time, having some benefit, so it is plausible to assume that the estimate is higher than 32.5%.

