## 8.2 Data Analysis

Patient characteristics will be summarized. Summaries of continuous variables will be presented as means and standard deviations if normally distributed, and as medians and inter-quartile ranges for skewed data, whilst categorical variables will be presented as frequencies and percentages. The difference between the two study groups in the proportion of patients achieving substantial improvement in the metabolic syndrome both at 12 and 18 months will be analysed using logistic regression adjusting for the stratification variables (BMI groups and sites). Analysis of secondary outcomes will be conducted using standard statistical procedures applicable to categorical or continuous data as appropriate. For missing values we will explore the pattern and the extent of missingness and we will carry out an appropriate form of multiple imputation if required. The analysis will be performed according to the intention to treat principle. All statistical tests will be two-tailed with a 5% significance level.

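### Patients whose device is removed early have no scheduled HbA1c near 12 months, and those removed before Month 3 have none at 18 months

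*Protocol*

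**What the plan says.** All references are to the Protocol.

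- **Endpoint and analysis.** Section 2.4 gives a 20% reduction in HbA1c as the primary endpoint, without a time point. Section 8.2 compares the arms at 12 and 18 months by logistic regression and adds: "The analysis will be performed according to the intention to treat principle". It allows multiple imputation if needed.
- **Blood schedule.** Section 5.5.10 makes Table 4 the definition of what is drawn: "See table below for a detailed description of blood collection at each visit". For columns V1, V3 and V5 to V15, the HbA1c row reads "HbA1C | x | | x | | x | x | x | x | | x | x | | x". It is marked at V1, V5, V7, V8, V9, V10, V12, V13 and V15, and is blank at V3, V6, V11 and V14.
- **Visits after removal.** For early removals, section 7.2 says "Subjects that have the device removed before Month 3 will return for the End of Treatment/Months 12 (visit 11"). For later ones it says "Subjects that have the device removed after Month 3 will return for the End of Treatment/Month 12 (visit 11), Month 15 (visit 12), Month 18" (V13), and then Month 24 (V15). Section 7.1 repeats both rules. V10 appears in neither list.
- **Fallback.** For subjects in either arm who withdrew early and had no follow-up arranged under the previous protocol version, section 7.2 adds a telephone contact at Month 24. It collects "HbA1 (provided through their last routine appointment at their GP").
- **Sample size.** Section 8.1 builds the device-arm rate on this premise: "If 30% of patients in the treatment group need to remove the device early but remain available for follow-up". It assigns those patients response rates of 15%, 23% and 31%, in thirds.

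**The concern.** The schedule does not collect the data that the sample size and the analysis rely on. A patient whose device comes out at, say, month 5 returns at 12 months and gives blood, but the primary outcome is not measured. The gap is tied to treatment failure and, as a matter of schedule, arises only in the device arm. If those patients drop out of the 12-month comparison, or are imputed as though they still had the device, the result moves from the diluted effect that section 8.1 plans for towards the undiluted one. That favours the device.

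**Working it through.** **1. Which HbA1c values are scheduled** (Table 2 timings, Table 4 draws, sections 7.1 and 7.2)

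| Patient | Near 12 months | 18 months | Other HbA1c after removal |
|---|---|---|---|
| On schedule, either arm | V10 (11.5 m) | V13 | not applicable |
| Removed between V10 and V11 | V10, already taken | V13 | V12, V15 |
| Removed after Month 3, before V10 | none (V11 has no HbA1c) | V13 | V12 (15 m), V15 (24 m) |
| Removed before Month 3 | none | none | none, except a GP value at Month 24 for some withdrawals |

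The blank V11 cell looks genuine. The row has all 13 cells, and the lipids row is also blank at V11.

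**2. The protocol's own figures reproduce**

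- Device-arm rate: 0.7 × 40% + 0.1 × (15% + 23% + 31%) = 28% + 6.9% = 34.9%, stated as 35%.
- Worst case, with removed patients responding at the control rate: 0.7 × 40% + 0.3 × 15% = 32.5%, as stated.
- Sample size for 35% vs 15%, two-sided 5%, 80% power, pooled variance, no continuity correction: 73 per group (power 80.3%), as stated. With 10% loss, 80 × 0.9 = 72 evaluable per group, power 79.8%.

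These figures need an observed outcome in the removed patients.

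**3. How many values could be missing**

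Section 8.1 says up to 30% early removal and notes lower rates elsewhere, so I take 10%, 20% and 30%. I assume that every removal precedes V10, and that the 10% ordinary loss applies to the remaining device patients and to the controls.

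| Removal rate | Device patients with no scheduled 12-month value | Device outcomes missing, with ordinary loss | Control outcomes missing |
|---|---|---|---|
| 10% | 8 of 80 | 0.10 + 0.90 × 0.10 = 19% | 10% |
| 20% | 16 of 80 | 0.20 + 0.80 × 0.10 = 28% | 10% |
| 30% | 24 of 80 | 0.30 + 0.70 × 0.10 = 37% | 10% |

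**4. Size of the bias if removal is ignored**

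Retained patients alone respond at 40%, an apparent difference from control of 25 points. The intention-to-treat device rate is (1 − e) × 40% + e × r, where e is the removal rate and r the response rate in removed patients.

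| e | True difference, r = 23% (the 8.1 average) | Overstated by | True difference, r = 15% (worst case) | Overstated by |
|---|---|---|---|---|
| 10% | 38.3 − 15 = 23.3 | 1.7 | 37.5 − 15 = 22.5 | 2.5 |
| 20% | 36.6 − 15 = 21.6 | 3.4 | 35.0 − 15 = 20.0 | 5.0 |
| 30% | 34.9 − 15 = 19.9 | 5.1 | 32.5 − 15 = 17.5 | 7.5 |

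**5. The opposite choice also costs**

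Counting every removed patient as a failure gives 0.7 × 40% = 28% vs 15% at 30% removals. Power at 72 per arm is then about 48%.

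**The case against.** Several stronger readings are tempting, and the documents do not support them.

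- **That nobody has a 12-month HbA1c.** V10 is at 11.5 months and V11 at 12 months, each ±7 days. V10 falls just before planned removal and can serve as the 12-month value. The defect concerns removed patients only.
- **That outcome data are missing only in the device arm.** Section 8.1 allows 10% loss to follow-up, and section 7.2 covers early withdrawals in both arms. Only the scheduled gap is specific to the device arm.
- **That 24 patients, and 5 to 7.5 points, are the expected result.** They need the top of the 30% range, every removal before V10, and an analysis that ignores removal. The documents do not divide removals into before and after Month 3.
- **That imputation must return 40%.** Section 8.2 promises to explore the missingness and choose a suitable method, and the details may sit in an analysis plan not shown. A model using removal status, on-device values and the 15, 18 and 24-month values would reduce the bias for removals after Month 3. For removals before Month 3 it has no scheduled value after removal to work from.

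It can also be said that sections 7.1 and 7.2 do not forbid V10, and that the post-removal treatment text in section 5.5.2 refers to an HbA1c level and so presupposes some measurement. Both are true, but neither schedules a value near 12 months. A GP result obtained at Month 24 cannot stand in for one.

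Finally, section 8.2 words its 12- and 18-month outcome as improvement in the metabolic syndrome, not as HbA1c. I read it as the primary endpoint because section 2.1 defines the metabolic objective by the 20% HbA1c reduction. The point rests on that reading.

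**Conclusion.** The point stands for removed patients. A device removed before V10 leaves no scheduled HbA1c near 12 months, and a removal before Month 3 leaves none at 18 months. This conflicts with the follow-up premise in section 8.1 and with intention to treat at both time points in section 8.2.

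At 12 months the upper bounds are 24 of 80 device patients without a value and an overstatement of about 5 points, or 7.5 if removed patients respond like controls. At 10% removals these fall to 8 patients and 1.7 to 2.5 points. At 18 months the gap is confined to removals before Month 3, whose number cannot be derived from the documents. It should be corrected in the protocol, because no analysis plan can recover a sample that was never taken.

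**What to change.** 1. In Table 4, add HbA1c to the existing V11 blood draw, at least for patients whose device was removed early. Alternatively, list V10 for them in sections 7.1 and 7.2.
2. Define the 12-month value as V10, or V11 if V10 is absent.
3. Amend sections 7.1 and 7.2 so that removals before Month 3 also have an HbA1c at Month 18, at V13 or from the nearest GP result.
4. For patients already past these visits, seek with their permission the GP HbA1c nearest 12 and 18 months. Section 7.2 already accepts a GP result as a source.

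The cost is one assay on blood already being taken, one added visit or GP request for each removal before Month 3 (V13 is not currently on their list), and an amendment with ethics approval. Part of the recovery would be retrospective.

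### Section 7.2 recalls patients whose device is removed before Month 3 for Visit 11 only, so as written they have no scheduled Month 18 HbA1c

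*Protocol*

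**What the plan says.** Section 7.2 of the protocol sets two return schedules by date of removal. For early removals it says "Subjects that have the device removed before Month 3 will return for the End of Treatment/Months 12 (visit 11". For removals after Month 3 it lists Visit 11 and then "Month 15 (visit 12), Month 18 (visit 13) and Month 24 (visit 15) post explant follow-up visits". A further paragraph provides a telephone consultation at Month 24, which collects adverse events, weight, medication changes and the last GP HbA1c. It applies to subjects who left the study early and "where no follow-up visit has been agreed or arranged as part of the previous protocol version (V4.1".

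Section 7.1, on stopping the whole study early, carries the same visit sentence ("Subjects that have the device removed before Month 3 will return for the End of Treatment/Month 12 (visit 11"). It also asks for the Visit 12 assessments in each subject, as far as possible.

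The HbA1c schedule is in section 5.5.10 ("Table 4. Summary of blood tests at each study visit"). Section 8.2 states that improvement in the "metabolic syndrome both at 12 and 18 months will be analysed using logistic regression", and that "The analysis will be performed according to the intention to treat principle". I read this as the primary response, which sections 2.1 and 2.4 define by a 20% fall in HbA1c. Section 8.1 bases the diluted 35% device rate on patients who "need to remove the device early but remain available for follow-up".

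**The concern.** Patients whose device comes out in the first three months have had the least exposure and probably the least benefit. Section 7.2 gives this group, and no other, a return schedule without a Month 18 visit. An intention-to-treat comparison at Month 18 needs their HbA1c, and the sample size reasoning assumes that removed patients can still be followed.

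The missingness is written into the protocol and linked to treatment failure. A statistical analysis plan cannot recover values that the protocol does not schedule. Section 8.2 allows multiple imputation if required, but there would be no scheduled Month 18 HbA1c from any removal before Month 3 to inform it. The imputed values would have to be borrowed from later removals, completers or controls. Scheduled adverse event ascertainment after Month 12 is also thinner for the same patients.

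**Working it through.** **1. The schedule.** The rows below come from Table 4, Table 2 and section 7.2.

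| | V10 (11.5 m) | V11 (12 m) | V12 (15 m) | V13 (18 m) | V14 (23 m) | V15 (24 m) |
|---|---|---|---|---|---|---|
| HbA1c, Table 4 | yes | no | yes | yes | no | yes |
| AE reporting, Table 2 | yes | yes | yes | yes | yes | yes |
| 7.2, removal before Month 3 | not listed | listed | not listed | not listed | not listed | not listed |
| 7.2, removal after Month 3 | not listed | listed | listed | listed | not listed | listed |

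HbA1c measurements listed after Month 12 are 0 for removals before Month 3, 3 for later removals (V12, V13, V15) and 3 for completers and controls. AE visits listed from Month 12 on are 1, 4 and 5 respectively, not counting the Month 24 telephone call.

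The Month 18 gap arises because Visit 13 is off the list. Visit 11 has no HbA1c for any patient in either arm; the point is only that the one visit left to early removals cannot supply a value.

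**2. Month 12.** The HbA1c nearest to Month 12 is at Visit 10, which is on neither return list. Section 7.2 does not say whether Table 2 visits continue up to Month 12 after removal. The Table 2 footnote, which applies X to all patients unless stated otherwise, suggests that they may.

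**3. The protocol's planning figures.** For 35% against 15%, two-sided 5%, 80% power and pooled variance, with mean rate 0.25:

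n = [1.96 × √(2 × 0.25 × 0.75) + 0.842 × √(0.35 × 0.65 + 0.15 × 0.85)]² / 0.20² = 72.4, so 73 per group, as stated.

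The dilution also reproduces: 0.7 × 40% + 0.3 × (15% + 23% + 31%)/3 = 34.9%, stated as 35%.

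**4. Possible size of the Month 18 gap.** The protocol gives no count of removals before Month 3, so the following are assumptions.
- Ceiling: 30% of 80 = 24 early removals in all.
- Removals spread evenly over 12 months: 24 × 3/12 = 6.
- The third of removals that section 8.1 assumes to respond at the control rate: 24/3 = 8, which is 10% of the arm. Section 8.1 does not tie this third to removal before Month 3; that link is mine.

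The possible range is 0 to 24.

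**5. Effect on a complete-case device rate**, taking the planning rates to hold at Month 18. Expected responders are 0.35 × 80 = 28.
- 6 missing at 15%: (28 − 0.9)/74 = 36.6%, up 1.6 points.
- 8 missing at 15%: (28 − 1.2)/72 = 37.2%, up 2.2 points, or 11% of the planned 20-point difference. Starting from the unrounded 34.9% gives 37.1%.
- All 24 missing: the 56 remaining patients at 40%, up 5 points.

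**The case against.** The best defence is that section 7.2 is ambiguous rather than wrong. The visit lists follow a sentence about subjects who withdraw from the study with a device in place. Read as covering study withdrawals only, the fair comparator is a withdrawn control, for whom 7.2 lists no return visit and offers only the Month 24 call. Read as covering patients who stay in the study, the Table 2 footnote and the intention-to-treat rule favour continued visits.

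The ambiguity is real for the period before Month 12. It does not remove the Month 18 gap, because separate lists for removal before and after Month 3 have no meaning unless early removals skip Visits 12, 13 and 15.

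Other parts of the defence stand and limit the point. A reader might infer any of the following, and the documents do not support them:
- **That the Month 24 contact is lost for every early removal.** The telephone call covers early withdrawals with no visit arranged under V4.1. It does not clearly reach those with a visit already arranged, or those explanted who remain in the study, and it schedules no Month 18 value.
- **That section 7.1 leaves the same gap.** Its request for Visit 12 assessments brings an HbA1c and an adverse event review at Month 15, so the gap there is smaller.
- **That the Month 12 HbA1c is certainly lost.** The text leaves this open.
- **That serious events would go unrecorded.** Section 6.1 has serious events recorded throughout the study, section 6 requires all adverse events to be recorded, and section 5.4 requires a form whenever an investigator is notified of one. What is reduced is scheduled ascertainment.
- **That the trial result is biased by a known amount.** The 40% rate comes from patients who reached a year with the device in place. If benefit fades after removal, the Month 18 bias shrinks. It also presupposes a complete-case analysis, which section 8.2 does not prescribe.

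**Conclusion.** The point holds in a limited form. The return rule for removals before Month 3 omits the Month 18 HbA1c and the scheduled Month 15 and Month 18 adverse event visits, without a stated reason. This conflicts with the intention-to-treat analysis at 12 and 18 months and with the follow-up assumption in section 8.1. Month 24 is partly covered.

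The direction of any bias, towards the device in a complete-case analysis, rests on early removals responding less often than the rest of the arm. The size is unknown. The move from 35% to about 37% assumes 8 removals before Month 3, a 15% response among them, and 12-month planning rates that still apply at Month 18. The planned sample size is not in question. This is a cheap improvement that should be made, not a defect that undermines the trial.

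**What to change.** In sections 7.1 and 7.2, replace the two lists with one rule: every early removal, whatever its date, has Visit 11 and the Month 15, 18 and 24 visits already listed for later removals. If the patient will not attend, make a telephone contact and obtain a GP HbA1c, with consent. State also that the Visit 10 HbA1c is kept for all explanted subjects.

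The cost is about three contacts per removal before Month 3: 18 for 6 patients, 24 for 8, and 72 at the ceiling of 24. No new visit type is needed and the sample size does not change. Some patients may decline, and those who have left the study would have to agree to the contacts, as section 7.2 already requires for the Month 24 call.
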